## 5.2. Exclusion Criteria

- Neuroendocrine histology of any kind
- Sarcoma or sarcomatous components in the histology
- Tumors that originate from bony metastases without a soft tissue component, or tumors if which the soft tissue component constitutes less than 50% of the total tumor volume, or if the soft tissue component is unlikely to contribute to the target symptom

- Unable to complete study questionnaires
- Ongoing treatment with an investigational drug at inclusion
- Planned inclusion in another interventional clinical study within 4 weeks after radiotherapy
- Pregnancy (due to risk of teratogenic and abortifacient effects of radiotherapy)

### **5.3. Lifestyle Considerations**

Current smoking will be recorded in the electronic case report form (eCRF) as it can affect the radiotherapy response. However, no restrictions regarding smoking will be applied. No other lifestyle considerations are applicable.

### **5.4. Screen Failures**

Screen failures are defined as patients who consent to participate in the clinical study but are not subsequently randomized to either of the study arms. A minimal set of screen failure information is required to ensure transparent reporting of screen failure participants to meet the Consolidated Standards of Reporting Trials (CONSORT) publishing requirements and to respond to queries from regulatory authorities. Minimal information includes demography, screen failure details, eligibility criteria, and any SAE.

Patients who do not meet the inclusion criterion of  $\geq 4$  points on a NRS- scale of 0-10 may be rescreened at a later point if symptoms deteriorates.

### **5.5. Criteria for Temporarily Delaying**

If the intervention in arm B must be paused due to toxicities or other concerns, a maximum radiotherapy period of 10 weekdays is allowed. The decision of temporary treatment delay relies upon the local clinical oncologist.

## 6. Study Intervention(s) and Concomitant Therapy

Study intervention is defined as any investigational intervention(s), marketed product(s), placebo, or medical device(s) intended to be administered to a study participant according to the study protocol.

The study intervention in this study is radiotherapy delivered in two different schedules

### 6.1. Study Intervention

|                                                       | Arm A        |         | Arm B        |
|-------------------------------------------------------|--------------|---------|--------------|
| Intervention Name                              | Radiotherapy |         | Radiotherapy |
| Dose/fraction                                  | 8 Gy         |         | 5 Gy         |
| Total number of fractions                      | 1            | 2       | 5            |
| Fractions per day                              | 1            | 1       | 1            |
| Total radiation dose in EQD2a       |              |         |              |
| Tumor (<math>\alpha/\beta</math> of 10)        | 12 Gy        | 24 Gy   | 31.25 Gy     |
| Normal tissue (<math>\alpha/\beta</math> of 3) | 17.6 Gy      | 35,2 Gy | 40 Gy        |

a Equivalent dose in 2 Gy fractions

### 6.2. Radiotherapy planning

The radiotherapy planning and delivery will be performed according to institutional practice at each participating site without study specific adjustments. However, contouring of nearby surrounding normal tissue/organs will be required as defined in the table below.

If a second fraction is offered to patients in arm A ([section 4.3.1](#)), a cone beam Computed Tomography (CBCT) is recommended for control of positioning. Alternatively, kV/kV may be applied if decided sufficient. The date of the CBCT (or kV/kV) should be recorded in the eCRF. If the local clinical oncologist considers replanning necessary, the reason for this should be recorded in the eCRF.

The following dose/volume parameters should be recorded in the eCRF.

|               | Volume (cm  ) | Dose (Gy) (nominal)                          | Definition                                                                                                   |
|---------------|---------------------------|----------------------------------------------|--------------------------------------------------------------------------------------------------------------|
| Target | GTV                       |                                              | Gross tumor volume                                                                                           |
|               | CTV                       | CTV D98 (Gy)                                 | Clinical target volume                                                                                       |
|               | PTV                       | PTV D95 (Gy)                                 | Planning target volume                                                                                       |
|               |                           | PTV D min (Gy) (point dose)       |                                                                                                              |
|               |                           | PTV D max (Gy) (point dose)       |                                                                                                              |
| OAR    | Bladder                   | Average/mean dose (Gy)                       | Whole organ                                                                                                  |
|               |                           | D max (0.1 cm  ) (Gy) |                                                                                                              |
|               | Rectum                    | Average/mean dose (Gy)                       | From top of anal canal to the rectosigmoid transition                                                        |
|               |                           | D max (0.1 cm  ) (Gy) |                                                                                                              |
|               | Anal canal                | Average/mean dose (Gy)                       | 3 cm from anus in axial plane                                                                                |
|               |                           | D max (0.1 cm  ) (Gy) |                                                                                                              |
|               | Bowel bag                 | Average/mean dose (Gy)                       | Intraperitoneal space from 2 cm above the upper limit of PTV to 2 cm below lower limit of PTV in axial plane |
|               |                           | D max (0.1 cm  ) (Gy) |                                                                                                              |

If target volume has a skeletal component (below 50 % according to exclusion criteria), this will be recorded in the eCRF.

### 6.3. Measures to Minimize Bias: Randomization and Blinding

During the screening period, patients will be assigned a unique identity number in the screening log in ascending numerical order at each study site. At randomization, each patient will be assigned a unique treatment number (randomization number) in the eCRF.

Treatment number encodes the patient's allocation to one of the two study arms according to the randomization schedule.

This is an open-label study. Potential biases will be reduced by central randomization. Patients will be randomly assigned to one of the radiotherapy courses by an allocation ratio 1:1.

Randomization will be conducted using stratified block randomization by target symptom.

#### **6.4. Study Intervention Compliance**

Patients will only receive study intervention at the radiotherapy unit by designated staff (radiation therapists) and under medical supervision. The date and time of each radiotherapy fraction will be recorded in the source documents using radiotherapy software (OIS=Oncology Imaging System) at each unit. The correct study intervention (radiation dose per fraction and number of fractions) and the study participant identification, will be confirmed at the time of the first radiotherapy fraction by a member of the study site staff or a designated radiation therapist.

#### **6.5. Radiotherapy Treatment Course Modification**

The radiotherapy course of patients in arm B can be modified during the intervention if considered necessary by the local clinical oncologist. Modifications include fractionation changes or intervention pauses, and may be initiated as a result of extensive toxicity, deterioration in the general condition of the patient or poor patient compliance. In case of fractionation changes, the total nominal radiation dose received and number of radiotherapy fractions will be recorded in the eCRF. The patient may continue participation in the study if appropriate. If the radiotherapy is paused, a maximum radiotherapy duration of 10 weekdays is allowed, otherwise the intervention must be recorded as incomplete in the eCRF. A patient can resume intervention if considered appropriate by the local clinical oncologist.

If radiotherapy schedule modifications are deemed necessary prior to radiotherapy start in either study arm, the patient must be discontinued from the study.

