## **7. Discontinuation of Study Intervention and Participant Discontinuation/Withdrawal**

### **7.1. Discontinuation of Study Intervention**

It may be necessary for patients in arm B to permanently discontinue study intervention (i.e. radiotherapy), ([Section 6.5](#)). If study intervention is permanently discontinued, the patient may remain in the study to be evaluated for the planned assessments if the patient has not withdrawn the written consent. See the SoA ([Section 1.2](#)) for data to be collected at the time of discontinuation of study intervention and follow-up and further evaluations.

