### **7.2. Participant Discontinuation/Withdrawal from the Study**

- A patient may withdraw from the study at any time at his/her own request or may be withdrawn at any time at the discretion of the investigator for safety, behavioral, or compliance reasons. This is expected to be uncommon.
- At the time of discontinuing from the study, if possible, an early discontinuation visit should be conducted, as shown in the SoA. See SoA ([Section 1.2](#)) for data to be collected at the time of study discontinuation.
- The patient will be permanently discontinued from both the study intervention and the study at that time.
- If the patient withdraws the consent for disclosure of future information, the sponsor may retain and continue to use any data collected before such a withdrawal of consent.
- If a patient withdraws from the study, he/she may request destruction of any samples taken and not tested, and the investigator must document this in the site study records.

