## 9.4. Analysis Sets

The following six analysis sets are defined:

- Intention-to-treat (ITT) set
  - All randomized participants with a signed informed consent form
- Full-analysis (FA) set
  - All randomized, eligible participants with a signed informed consent form who has received at least one radiation fraction
- Per-protocol (PP) set
  - All randomized, eligible participants with a signed informed consent form who has received the allocated radiotherapy and completed the follow-up visits at 4 and 12, and 52 weeks without major protocol deviations
- Modified PP set 1
  - All randomized, eligible participants with a signed informed consent form who has received the allocated radiotherapy and completed the follow-up visits at 4 and 12 weeks without major protocol deviations
- Modified PP set 2
  - All randomized, eligible participants with a signed informed consent form who has received the allocated radiotherapy and completed the follow-up visit at 4 weeks without major protocol deviations
- Safety set
  - All randomized participants exposed to radiotherapy

As this is a non-inferiority study, the main analysis of the primary endpoint will be based on the modified PP set 1 of participants having completed all scheduled follow-up visits at the time of assessment (12 weeks).

The main analyses of the secondary endpoints of physician-reported toxicities (CTCAE) at 4, 12, and 52 weeks will be based on the modified PP set 2, modified PP set 1, and PP set, respectively. Safety analyses of physician-reported toxicities will be based in the safety set.

The main analyses of the secondary endpoint of overall survival will be based on the FA set.

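### Section 6.5 removes from the study, not only from the intervention, any randomised patient whose schedule is changed before the first fraction, so the ITT set lacks their 12-week outcome

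*Protocol*

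**What the plan says.** Section 6.5 (Radiotherapy Treatment Course Modification) sets the rule: "If radiotherapy schedule modifications are deemed necessary prior to radiotherapy start in either study arm, the patient must be discontinued from the study". Section 7.2 spells out what leaving the study entails: "The patient will be permanently discontinued from both the study intervention and the study at that time". The only further contact it foresees is this: "At the time of discontinuing from the study, if possible, an early discontinuation visit should be conducted, as shown in the SoA". Section 4.1 and the synopsis censor overall survival at study withdrawal.

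Once treatment has begun, the rule is different. For an arm B course changed during treatment, section 6.5 says: "The patient may continue participation in the study if appropriate". For permanent discontinuation of the intervention, again written for arm B, section 7.1 says that "the patient may remain in the study to be evaluated for the planned assessments if the patient has not withdrawn the written consent".

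On bias control, section 6.3 says: "This is an open-label study. Potential biases will be reduced by central randomization". Section 9.4 defines the ITT set as "All randomized participants with a signed informed consent form", and bases the main analysis of the primary endpoint on modified PP set 1.

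**The concern.** The protocol already separates stopping treatment from stopping follow-up, but only after the first fraction. It drops that separation in the interval between open-label randomisation and the start of treatment. There the oncologist can know the arm, and the schedules differ widely (one fraction of 8 Gy at first, against five of 5 Gy). Central randomisation protects the assignment itself. It does not protect against removals decided after the assignment is known.

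The main analysis is per-protocol. The usual safeguard for a non-inferiority claim on such a set is to see whether it also holds among all randomised patients. That safeguard needs 12-week NRS values from patients who did not receive the allocated schedule, and the sentence in section 6.5 stops their collection for one such group. A statistical analysis plan cannot recover values that were never collected, so the matter belongs in the protocol.

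**Working it through.** **1. Timing.** The Schedule of Activities puts randomisation in the preparation phase, before day 1, with screening and preparation spanning up to 28 days. The rule refers to patients in either arm before radiotherapy starts. A patient has an arm only once randomised, so the rule acts after allocation. With no masking, the arm can be known.

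**2. The two situations side by side.**

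| | Change before first fraction | Arm B course changed or stopped after start |
|---|---|---|
| Source | 6.5, last paragraph; 7.2 | 6.5, first paragraph; 7.1 |
| Intervention | Ends | Modified or ends |
| Study participation | Must end | May continue |
| Scheduled NRS and CTCAE | Stop; early discontinuation visit where feasible | Continue |
| Survival | Censored at withdrawal | Followed |

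The Schedule of Activities, as reproduced, has no column for an early discontinuation visit. No other section keeps the pre-start group in follow-up.

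**3. Effect on each analysis set in section 9.4.**

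| Set | Use | Patient changed before start |
|---|---|---|
| Modified PP set 1 | Primary endpoint; 12-week toxicity | Out, because the allocated radiotherapy was not received; followed or not makes no difference |
| Modified PP set 2 and PP set | Toxicity at 4 and 52 weeks | Out, for the same reason |
| FA set | Overall survival | Unclear: one or more fractions are required, without saying whether a fraction given off study counts |
| ITT set | No analysis named | In, but without a scheduled 12-week NRS |

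The change to the rule therefore matters for the ITT set and for completeness of survival data. It does not alter the main primary or toxicity analyses.

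**4. Design figures.** Section 9.3 gives SD 2, margin 1, one-sided 2.5% and power 85%. With 73 per arm the noncentrality is 1 / (2 × √(2/73)) = 3.02 on 144 degrees of freedom, and the noncentral t gives power 0.851. Hence 2 × 73 = 146, as stated. Allowing for 25% exclusion, 146 / 0.75 = 194.7, or 195, against the stated 200. This point changes none of these figures.

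**5. Scale.** At 1:1, 200 / 2 = 100 patients per arm, so each pre-start removal is 1% of an arm in the ITT set. The plan expects 146 of 200 in the per-protocol population, so 200 − 146 = 54 patients (54 / 200 = 27%) may fall outside it. The pre-start group is an unknown part of those 54; the protocol gives no expected number.

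**The case against.** The strongest reply is that nothing in the main results depends on this rule. Modified PP set 1 requires the allocated radiotherapy, and the toxicity analyses by time point also use per-protocol sets. The protocol names no analysis on the ITT set and defers detail to a statistical analysis plan. That stands, and it limits the point to the supportive analysis and to survival.

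Several further replies also stand in part:
- Patients must be candidates for both schedules at entry, both schedules are in routine use, and arm A allows a second fraction. This lowers the chance that knowledge of the arm prompts a change, but it does not remove it.
- Not everything is lost. Baseline NRS must exist before randomisation, section 7.2 lets data already collected be kept, and section 8.1 records the date and cause of going off study and the cause of death. An imbalance in removals would therefore be visible, but the 12-week outcomes would still be missing.
- Missing-data methods could be applied in the ITT set. For this group they would rest on assumptions that the trial's own data cannot test.

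A reader might infer that the rule pushes the primary result towards non-inferiority by taking poor responders out of arm A. The protocol does not support this. The per-protocol definition excludes these patients in any case, and no direction is given. Removing frail patients from arm B, for example, would work the other way.

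**Conclusion.** The point holds as a low-cost improvement to data collection. Section 6.5 treats a schedule change before the first fraction more severely than one after it, and ends scheduled post-baseline NRS, CTCAE and survival follow-up for a randomised patient. As a result, the per-protocol non-inferiority conclusion cannot be checked against observed 12-week NRS in all randomised patients, and survival is cut short for this group.

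The effect on the main primary estimate is nil. The effect on an ITT analysis cannot be sized, because the protocol gives neither the number of such patients nor their likely outcomes. That removals are driven by the allocation is a possibility that follows from the open-label timing, not something the protocol states. Nor is it established that these patients always drop out of the survival analysis, because the FA definition leaves this open.

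**What to change.** Reconcile section 6.5 with section 7.1 by distinguishing discontinuation of the study intervention from discontinuation of the study, in both arms. Patients whose schedule is changed before the first fraction would, unless they withdraw consent:
- keep the scheduled NRS, CTCAE and survival assessments, counted in the arm to which they were randomised;
- have the schedule actually given and the reason for the change recorded;
- stay outside the per-protocol sets;
- be included in a supportive ITT analysis of the primary endpoint and of overall survival.

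The cost is a short amendment to section 6.5, a line naming the supportive ITT analysis, and follow-up of a few extra patients. The sample size of 146 evaluable and 200 randomised is unchanged, and no treatment decision is affected.

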#### **6.6. Continued Access to Study Intervention after the End of the Study**

After the 12-week follow-up visit, patients will resume to ordinary follow-up visits at their local cancer department. Patients may receive additional radiotherapy treatment within the same PTV after completion of study-specific follow-up visit at 4 weeks, but the following should be recorded in the eCRF:

- Radiation treatment within the same PTV until the 52 week follow-up visit.

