Abbreviations: AE=Adverse Event, CT= Computed Tomography, CTCAE= Common Terminology Criteria Adverse Events, CRP= C-reactive protein, ECOG = Eastern Cooperative Oncology Group, EORTC QLQ-C15 PAL= European Organization for the Research and Treatment of Cancer Quality of Life Questionnaire-Core15 Palliative, GPS= Glasgow Prognostic Score, LDH=Lactate dehydrogenase, NRS=Numerical Rating Scale, SAE=Serious Adverse Event, WOCBP=Women of childbearing potential

a All follow-up is defined from the day of completed radiotherapy (arm A: D1, arm B: D5 or D6-10 if modifications, see Section 6.5)

b If a second fraction is offered (see [Section 4.3.1](#)), evaluation must be scheduled 4 weeks +/- 4 days after the second fraction is delivered,. For all other patients, evaluations must be scheduled 8 weeks +/- 4 days from baseline

c Within 72 hours before randomization

d Only if baseline NRS score of target symptom is available

e Including pain medication, tranexamic acid, anticoagulants, laxatives, antidiarrheal medication, antiemetics and steroids

f Radiotherapy treatment within the same planning target volume (PTV) (additional fraction after 4 weeks in arm A is not considered reirradiation)

g I.e. hospital submissions and coding record related to radiotherapy

h All AE ≥grade 3/SAE

i Only AE ≥grade 3/SAE with suspected causality with radiotherapy

j To be performed within 4 days after decision

k Only if second fraction is offered. See [Section 4.3.1](#)

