### **2.1.1. Principal Research Question**

The principal research question is whether radiotherapy with 1-2 fractions of 8 Gy (arm A) provide non-inferior patient-reported target symptom relief as compared to a more prolonged radiotherapy schedule with 5 fractions of 5 Gy (arm B) in patients with symptomatic pelvic soft tissue tumors, assessed after 12 weeks of follow-up. The target symptom is the patient-reported main complaint according to study-specific predefined categories (pain, bleeding, bowel dysfunction, lower urinary tract dysfunction or vaginal dysfunction).

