### 3. Objectives, Endpoints and Assessments

#### **Primary objective**

*Assess whether 1-2 fractions of 8 Gy is non-inferior to 5 fractions of 5 Gy with respect to target symptom relief.*

Endpoint: Change in the average (last 24 hours) patient-reported target symptom intensity from baseline (BL) assessed after 12 weeks of follow -up

Assessment: Numerical Rating Scale (NRS) score (0-10)

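### Further radiotherapy to the same target volume is allowed from week 4, and the primary analysis does not say how a week-12 score obtained after it is used

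*Protocol*

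**What the plan says.** The principal research question (Protocol 2.1.1) is whether 1-2 fractions of 8 Gy "provide non-inferior patient-reported target symptom relief as compared to a more prolonged radiotherapy schedule with 5 fractions of 5 Gy", judged at 12 weeks. Section 3 gives the endpoint as "Change in the average (last 24 hours) patient-reported target symptom intensity from baseline (BL) assessed after 12 weeks of follow -up".

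Section 6.6 then provides: "Patients may receive additional radiotherapy treatment within the same PTV after completion of study-specific follow-up visit at 4 weeks". It names no arm. Its only requirement is an eCRF entry for "Radiation treatment within the same PTV until the 52 week follow-up visit".

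In the Schedule of Activities (1.2), footnote f says of this record that the "additional fraction after 4 weeks in arm A is not considered reirradiation". So the protocol itself separates re-irradiation from the 1-2 fraction strategy under test.

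On analysis, section 9.4 says: "As this is a non-inferiority study, the main analysis of the primary endpoint will be based on the modified PP set 1". Members of that set must have "received the allocated radiotherapy and completed the follow-up visits at 4 and 12 weeks without major protocol deviations". Section 9.5.2 fits a linear regression to the week-12 change and declares non-inferiority if the lower 95% bound is above -1. Neither section mentions radiotherapy given between weeks 4 and 12, and the term for major deviations is not defined.

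**The concern.** The trial compares two schedules by their effect at 12 weeks, yet a patient whose symptom has not responded may have the same volume irradiated again up to eight weeks before that measurement. A treatment that the protocol allows is not, on its face, a protocol deviation. Such a patient has had the allocated radiotherapy, attends weeks 4 and 12, and so appears to stay in modified PP set 1 with a score partly produced by something else.

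Re-irradiation follows randomization, depends on response, and is decided open label. The argument in section 2.1.4 that systemic treatment should be spread evenly by randomization therefore does not carry over. If one arm palliates less, it has more failures to re-treat, and their later improvement narrows the observed difference. In a non-inferiority trial that narrowing can favour the claim.

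Calling re-irradiation a major deviation does not solve this, because it removes the patients in whom the schedule failed. Section 9.2 ties a standard-of-care recommendation to the result, so what the week-12 score represents should be settled in advance.

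**Working it through.** **Inputs from the protocol (9.3, 9.5.2, 6.3).** SD 2; margin 1; one-sided 2.5%; power 85%; 146 evaluable, hence 73 per arm at 1:1; 200 randomized.

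**The plan's own figure.** The noncentral t test gives 85.1% power at 73 per arm and 84.6% at 72, so 146 is reproduced. Allowing for 25% exclusion, 146/0.75 = 195, against 200 stated.

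**Decision threshold.** SE = 2 × √(2/73) = 0.331. Non-inferiority is declared when the estimate exceeds -1 + 1.96 × 0.331 = -0.351.

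**Effect of re-irradiation.** Let rA and rB be the proportions re-irradiated before week 12 and g the NRS gain per re-irradiated patient. The observed difference moves by s = (rA - rB) × g. If arm A is truly worse by exactly 1 point,

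P(declare) = 1 - Φ((-0.351 + 1 - s)/0.331).

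The protocol gives none of rA, rB or g, so every row is an assumption:

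| Scenario | s | P(declare non-inferiority) |
|---|---|---|
| Equal rates, equal gain | 0 | 2.5% |
| 5 points more in A, gain 3 | 0.15 | 6.6% |
| 15 points more in A, gain 2 | 0.30 | 14.6% |
| 15 points more in A, gain 3 | 0.45 | 27.4% |
| 10 points more in B, gain 2 | -0.20 | 0.5% |

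**Same rule in both arms.** The fixed imbalances above are chosen, not derived. A more neutral check lets the imbalance arise from response. Improvement is simulated as normal with SD 2 and mean 3 in B and 2 in A. Failure is an improvement of at most 2 points, and the same share of failures is re-irradiated in each arm.

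| Share of failures re-irradiated | A / B re-irradiated | Gain 1 | Gain 2 | Gain 3 | Patients excluded instead |
|---|---|---|---|---|---|
| 20% | 10% / 6% | 3% | 4% | 6% | 3% |
| 40% | 20% / 12% | 4% | 7% | 12% | 4% |
| 60% | 30% / 19% | 6% | 13% | 23% | 7% |

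Excluding these patients also lifts the rate above 2.5%, though less than crediting a gain of 2 or 3 points.

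**Away from the margin.** With a true difference of -1.5, the same simulation gives at most 3.2%. The issue matters mainly for true differences near -1.

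**The case against.** **Retention is inferred.** No sentence says that these scores count. Section 9.5 calls itself a brief summary and defers detail to a SAP, which may handle the event. One could also read the allocated-radiotherapy condition as excluding anyone given more. This stands as a limit on the wording. Still, the protocol itself permits the event before the endpoint and fixes the primary set, and excluding these patients is not neutral either.

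**Later care may be part of the question.** The design is described as pragmatic, and arm A is already a strategy with response-triggered re-treatment. If the question is schedule plus usual later care, the observed week-12 difference is the true one and the percentages above are not error rates. That is a legitimate question. However, section 2.1.1 asks about the schedules, and section 9.4 chooses a per-protocol set because the trial is one of non-inferiority. The protocol should say which question it answers.

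**Direction is open.** A reader might infer that arm A will look non-inferior because its failures were re-treated. The documents do not support that. Arm A failures may first be offered the second 8 Gy fraction (4.3.1), which does not count as re-irradiation, whereas section 6.6 is the only route for arm B failures. Re-irradiation could be commoner in B and work against arm A. More use in A is plausible if A palliates less, since section 6.1 gives a tumor EQD2 of 12 or 24 Gy against 31.25 Gy, but it is not established.

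**Gains may be partial.** Section 2.1.4 says maximum response can take up to 12 weeks, so a gain of 2 or 3 points may not be fully expressed by week 12. This favours the lower end of the range.

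**Conclusion.** The point holds as a gap in what the primary comparison means, not as a demonstrated bias toward arm A. Section 6.6 permits an outcome-altering treatment eight weeks before the endpoint, and sections 9.4 and 9.5.2 contain nothing that stops the later score being read as the response to the allocated schedule.

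On the plan's own SD, margin and evaluable number, and with arm A truly at the margin, the false non-inferiority rate runs from 2.5% (equal use and gain) through about 4% to 12% (40% of failures re-irradiated under one rule, gain 1 to 3). Larger imbalances give more. The figures of 15% and 27% need an assumed 15-point excess in arm A and should not be taken as expected. All of these are error rates only if the target is the effect of the schedules without further radiotherapy.

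**What to change.** Leave clinical access under section 6.6 as it is and change sections 9.4 and 9.5.2:

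1. Name as an intercurrent event any radiotherapy to the same PTV before the week-12 assessment other than the allocated schedule, where the allocated schedule includes arm A's second fraction.
2. State that these patients are not dropped from the primary analysis.
3. Alongside the analysis of the observed week-12 NRS, prespecify one that does not credit the score after re-irradiation, for example using the last NRS before it, or no change from baseline if that is worse.
4. Require non-inferiority to hold in both analyses before it is claimed.
5. Report re-irradiation before week 12 by arm, with its date. Section 6.6 and the Schedule of Activities require the treatment to be recorded but name no date, so the eCRF should ask for one. A target-symptom NRS when re-irradiation is decided would help item 3.

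**Cost.** Some wording, a date field and possibly one NRS item. The claim becomes slightly harder to make.

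The analysis in item 3 should not stand alone. Arm A's second fraction is not scored as failure, while any re-treatment in arm B is. If 10 percentage points more of B than A were re-irradiated and each lost 2 points by the rule, arm B's mean would fall by 0.10 × 2 = 0.2. False non-inferiority at a true -1 would then rise from 2.5% to about 9%. That is the reason for requiring both analyses to agree.
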